## Objectives

To compare the mortality and post-intervention complications of a selection of common congenital anomalies involving the gastrointestinal tract in LMICs and HICs globally.To identify patient-level and hospital-level factors affecting outcomes that be modified to improve care.To establish a research collaboration consisting of children’s surgical care providers across the world to help enhance research capacity and to create a platform for ongoing collaborative research and intervention studies aimed at improving outcomes.To raise awareness and provide advocacy for neonatal and paediatric surgical care within global health prioritisation, planning, policy and funding.

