What type of anaesthesia was used for the primary intervention?	General anaesthesia with endotracheal tube, General anaesthesia with laryngeal airway, Ketamine anaesthesia, Spinal/caudal anaesthesia, Local anaesthesia only, No anaesthesia/just analgesia, No anaesthesia/no analgesia, Not applicable: no surgery or intervention undertaken.
Who undertook the anaesthetic for the primary intervention?	Anaesthetic doctor, Anaesthetic nurse, Medical officer, Surgeon, Other healthcare professional, No anaesthetic undertaken. If more than one of these personnel were present, please select the most senior.
Who undertook the primary intervention?	Paediatric surgeon (or junior with paediatric surgeon assisting/in the room), General surgeon (or junior with paediatric surgeon assisting/in the room), Junior doctor, medical officer or other (without a paediatric or general surgeon assisting/in the room), Trainee surgeon (without a paediatric or general surgeon assisting or in the room), Not applicable — no surgery or primary intervention undertaken.
Was a Surgical Safety Checklist used at the time of primary intervention?	Yes, No: but it was available, No: it was not available, Not applicable: a conservative primary intervention was undertaken, Not applicable: no surgery or primary intervention undertaken.
Total duration of antibiotics following primary intervention	In days (including the day of surgery and the day antibiotics were stopped. Include intravenous and oral antibiotics).
Did the patient receive a blood transfusion?	Yes: not cross-matched, Yes: cross-matched, No: not required, No: it was required but not available. Within 30 days of primary intervention or 30 days of presentation if no intervention was undertaken.
Did the patient require ventilation? If yes, for how long did the patient remain on ventilation?	Yes: and it was given, Yes: but it was not available, No. Within 30 days of primary intervention or 30 days of presentation if no intervention was undertaken. Please include all types of ventilation. In days (include all days on ventilation within 30 days of primary intervention or 30 days of presentation if no intervention was undertaken).

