Time to first enteral feed (post-primary intervention)	In days (include the day of primary intervention and the day of first enteral feed in the calculation). Enter 0 if enteral feeds were not commenced. Enter 999 if feeds were not stopped, for example, in patients with Hirschsprung's Disease managed conservatively. Include all types of enteral feeding — oral, nasogastric, gastrostomy and other.
Time to full enteral feeds (post-primary intervention)	In days (enter 0 if the patient died before reaching full enteral feeds or 30 if the patient had not reached full enteral feeds at 30 days post-primary intervention or 30 days following admission in patients who did not receive a primary intervention). Include all types of enteral feeding — oral, nasogastric, gastrostomy and other.
Did the patient require parenteral nutrition? If yes, for how long did the patient receive parenteral nutrition?	Yes and it was given, Yes and it was sometimes available but less than required, Yes but it was not available, No. In days. Include all days that the patient received parenteral nutrition (any volume) up until 30 days post-primary intervention or 30 days following presentation in patients who do not receive an intervention.

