### Data analysis

#### Patient and institutional data

Data will be analysed using Stata and SAS V.9.4 (Cary, North Carolina, USA). Missing data for the covariates will be analysed to determine whether it is related to the outcome and either complete-case analyses or multiple imputation techniques will be used for analyses accordingly.

Significant differences in mortality between LMICs and HICs will be determined for each of the study conditions using Χ^2^ analysis, or Fischer’s exact test if either group contains <10 patients. World Bank classification of low, middle and high income countries during the fiscal year 2018 will be used.^38^

Univariate logistic regression analyses will be conducted between covariates and the primary outcome of mortality. Based on the results, covariates with a p value <0.10 will be included in the multivariate model. The final multi-level multivariate logistic model will be determined using stepwise backward elimination to interventions and peri-operative factors affecting outcomes. Data will be adjusted for confounding factors and effect modifiers. Potential confounders include gestation age at birth, weight, time from birth to presentation and American Society of Anesthesiologists score at the time of primary intervention. Potential effect modifiers include administration of peri-operative antibiotics, fluid resuscitation, thermal control and provision of other condition-specific neonatal care such as parenteral nutrition in neonates with gastroschisis.

Multi-level multivariate logistic regression analysis will also be undertaken to identify institutional factors affecting mortality with adjustment for confounders. P<0.05 will be deemed significant.

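### The mortality models adjust for ASA score at the intervention and for parenteral nutrition recorded to day 30; this may bias the effects of earlier care and make later care look protective

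*Protocol article*

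**What the plan says.** The second objective is "To identify patient-level and hospital-level factors affecting outcomes that be modified to improve care". The model that serves it is described under Data analysis, Patient and institutional data:

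- Screening: "covariates with a p value <0.10 will be included in the multivariate model". The final multilevel model then comes from "stepwise backward elimination to interventions and peri-operative factors affecting outcomes".
- Adjustment: "Data will be adjusted for confounding factors and effect modifiers".
- The confounders named are weight and gestational age, together with "time from birth to presentation and American Society of Anesthesiologists score at the time of primary intervention", so ASA is among them.
- The care variables are given another role: "Potential effect modifiers include administration of peri-operative antibiotics, fluid resuscitation, thermal control and provision of other condition-specific neonatal care such as parenteral nutrition", the last of these for gastroschisis.
- A separate multilevel model looks at institutional factors, adjusted for confounders.

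Table 1 defines the variables. For parenteral nutrition days the instruction is "Include all days that the patient received parenteral nutrition (any volume) up until 30 days post-primary intervention", or to 30 days after presentation where there is no intervention. The section mentions no landmark, no time-dependent exposure and no rule that a covariate must precede the exposure being studied.

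**The concern.** The model is meant to find care that could be changed to save lives. For that purpose a covariate should be fixed before the exposure it adjusts. ASA at the intervention is a sound severity measure for what happens at the operation, but it also reflects how well the child was resuscitated beforehand. Holding it constant can remove part of the benefit of that earlier care, or distort it. Parenteral nutrition has the opposite timing problem: a child who dies early cannot receive it, so receipt partly records survival.

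At stake is which factors are put forward for improvement. Early resuscitation could look less useful than it is, and care delivered later could look useful when it is not.

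**Working it through.** The plan gives no figure for this point, so the check compares the timing of variables and then illustrates the possible size.

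**1. Order of events (Table 1 and Outcome measures)**

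| Item | When fixed or recorded |
|---|---|
| Sepsis, hypovolaemia, hypothermia | On arrival |
| Warming | Begun within 1 hour of arrival |
| Fluid bolus, antibiotics for sepsis | Within 1 hour or on the first day |
| ASA score | At the primary intervention, which may be up to 30 days after presentation |
| Parenteral nutrition | Up to 30 days after the intervention |
| Primary outcome | In-hospital death, capped at 30 days after the intervention |

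Warming, bolus and arrival antibiotics therefore normally come before ASA. Parenteral nutrition shares its window with the deaths.

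**2. Who has an ASA score.** Table 1 codes ASA as not applicable where there was no intervention. The inclusion criteria require palliative and no-care patients to be included, and the primary outcome is defined for patients without an intervention. An ASA-adjusted model must drop them or give them their own category. Dropping them also removes children who died before any intervention, which is an outcome of the early care under study. The missing-data plan (complete cases or multiple imputation) does not suit a value that is undefined rather than missing.

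**3. Illustration for ASA. All inputs are assumed.** Early care is allocated at random and lowers mean ASA by 0.5 or 1.0 class. The log odds of death rise by 0.8 per class. The direct log odds ratio of care is −0.2, so the direct OR is exp(−0.2) = 0.82.

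| Shift in ASA | Unmeasured severity | Total OR | ASA-adjusted OR |
|---|---|---|---|
| 0.5 | none | 0.58 | 0.82 |
| 1.0 | none | 0.40 | 0.83 |
| 0.5 | affects ASA and death | 0.64 | 1.00 |
| 1.0 | affects ASA and death | 0.47 | 1.21 |

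Without unmeasured severity, adjustment leaves roughly the direct effect only. With it, children who had the care and still share an ASA class with those who did not tend to be sicker, and the estimate can pass 1. In a simpler form, if half of an OR of 0.50 acts through ASA, the adjusted OR is exp(0.5 × ln 0.50) = 0.71; that only restates the assumed half.

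**4. Illustration for parenteral nutrition with no true effect.** Assume half of patients are at centres that give it from about day 3 to everyone then alive, equal mortality m at both kinds of centre, and a share e of deaths before day 3. For m, take 56.6% (416/735, gastroschisis, LMIC combined, Table 2).

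- Risk if received: m(1 − e)/(1 − em)
- Risk if not received: (0.5m + 0.5em)/(0.5 + 0.5em)
- The odds are m(1 − e)/(1 − m) and m(1 + e)/(1 − m), so OR = (1 − e)/(1 + e). Mortality cancels; only the timing of deaths matters.

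| e | Risk, received | Risk, not received | OR |
|---|---|---|---|
| 0.2 | 0.511 | 0.610 | 0.67 |
| 0.3 | 0.477 | 0.629 | 0.54 |
| 0.4 | 0.439 | 0.646 | 0.43 |

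A second set of assumptions points the same way. Nutrition is planned in 60%, the start day is exponential with mean 2 or 4, and deaths are exponential with mean day 5. The share of planned patients among the deaths who start before dying is q = (1/2)/(1/2 + 1/5) = 0.714, or (1/4)/(1/4 + 1/5) = 0.556. The spurious OR is [0.6q/(1 − 0.6q)]/(0.6/0.4) = 0.50 or 0.33.

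**5. Other 30-day items.** Table 1 sets time to full feeds to 0 if the child died first, so that variable encodes the outcome. Days of ventilation and "Total duration of antibiotics following primary intervention" also accrue only while the child lives. They carry the same risk if they are screened.

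**The case against.** Several points on the other side stand.

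- ASA is only a potential confounder, and for operator, anaesthetist and checklist use it is a legitimate severity covariate. A reader might infer that adjusting for ASA is wrong throughout; the documents do not support that. The order of bolus or antibiotics and ASA is normal rather than certain, since both may be given at any time on the first day.
- A reader might infer that the institutional model adjusts for antibiotics, fluids and warming. It does not say so: it adjusts for confounders, and those variables stand in the other list. ASA is a listed confounder, so only ASA raises the problem there.
- A reader might infer that every 30-day item in Table 1 will be screened. Table 1 is a data form, and the covariates to be screened are not listed. Of the 30-day items, only parenteral nutrition is named in the analysis section.
- The model is already aimed at interventions and peri-operative factors, so antibiotics, fluids and warming will be estimated as well as adjusted for. The label of effect modifier is loose, but by itself biases nothing.
- Bolus, sepsis antibiotics and warming are asked only of children with the matching arrival state. Adjusting for that same state adds nothing to that comparison, although the other two states still matter.
- The form separates parenteral nutrition that was needed but unavailable from nutrition not needed. Comparing given with unavailable would avoid much of the pooling in step 4. The plan does not fix that contrast, the form has no code for death before nutrition could start, and days received would still depend on survival.

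What remains is stated wording: an ASA score taken after much of the care of interest, and a survival-dependent care variable, are both named for adjustment. This is more than detail left to an analysis plan.

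**Conclusion.** The concern holds in this limited form. Following the text may bias the estimated effects of pre-intervention care, and of institutional factors acting through it, by adjusting for ASA. It may also make parenteral nutrition look protective without any effect. ASA adjustment further leaves untreated patients without a valid covariate value.

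The documents do not allow size or direction to be computed. The odds ratios above depend on assumed timing of deaths, start of nutrition, centre capability and strength of the ASA pathway. A pull towards the null is the simple case for ASA, but it is not assured, as the values of 1.00 and 1.21 show.

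The effect is confined to the search for modifiable factors under the second objective. The primary LMIC versus HIC comparison by chi-squared or Fisher's test, and the sample sizes in Table 2, do not depend on it. The change should be made before analysis.

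**What to change.** 1. Name the exposure for each model and adjust only for variables fixed before it.
2. For pre-intervention care and for institutional factors, adjust for severity at arrival using data already collected: gestation, weight, age at presentation, associated anomalies, and sepsis, hypovolaemia and hypothermia on arrival.
3. Keep ASA for models of factors acting at the intervention (operator, anaesthetist, checklist), or for a sensitivity analysis restricted to treated patients.
4. Analyse parenteral nutrition by hospital-level availability, or in a landmark analysis of patients alive at a fixed, pre-stated day. Availability could come from the institutional survey if it records this (its content is not shown), or from each hospital's not-available answers on the patient form.
5. Keep other survival-dependent 30-day variables, such as time to full feeds, out of the main mortality model.
6. Treat antibiotics, fluids and warming as exposures, and call them effect modifiers only where an interaction is tested.

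The cost is re-specified models, one sensitivity analysis and one landmark analysis, with no new patient data. The landmark analysis excludes early deaths, so it describes survivors to that day only and must be labelled so.

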### Outcome measures

The primary outcome is all-cause, in-hospital mortality.

For patient’s hospitalised for >30 days following primary intervention, a 30-day post-primary intervention mortality rate will be used. Those who do not receive a primary intervention, but remain alive and hospitalised at 30 days following primary admission, will have this time point used for recording their mortality status for the primary outcome. Primary outcome is defined in table 1.

**Table 1 T1:** Generic data points

Generic questions	Answers
During which month did the patient present to your hospital?	October, November, December, January, February, March, April. Please select the month that the patient presented to your hospital for the first time with this congenital anomaly. For example, if a baby was born with gastroschisis on the 29 September and presented to your hospital on 1 October you should select October.
Has consent been provided to include this patient in the study? If no, which condition did the patient present with?	Yes, No, Patient consent is not required for this study at my institution. Oesophageal atresia, Congenital diaphragmatic hernia, Intestinal atresia, Gastroschisis, Exomphalos, Omphalocele, Anorectal malformation, Hirschsprung's Disease. Please select all the conditions that the patient presented with. Do not select a condition which the patient has already received surgical treatment for previously.

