Did the patient receive central venous access? If yes, did the patient acquire central line sepsis?	Yes: umbilical catheter, Yes: peripherally inserted central catheter, Yes: percutaneously inserted central line with ultrasound guidance, Yes: surgically placed central line (open insertion), No. Please select all that the patient received within 30 days of primary intervention or 30 days of presentation if no intervention was undertaken. Yes: diagnosed clinically, Yes: confirmed on microbiology, No. Within 30 days of primary intervention or 30 days of presentation if no intervention was undertaken.
Time from arrival at your hospital to primary intervention in hours	Enter 0 if no intervention was undertaken. *Primary intervention for each condition is defined as follows.* *Oesophageal atresia*: surgery, either temporising or definitive, to manage the oesophageal atresia and/or tracheo-oesophageal fistula. *Congenital diaphragmatic hernia*: surgery to reduce the hernia and close the defect. *Intestinal atresia*: surgery, either temporising or definitive, to manage the obstruction including stoma formation and primary anastomosis. *Gastroschisis*: any procedure to either cover or reduce the bowel and/or close the defect. This includes application of a silo (regardless of whether or not they go on to require surgery). It excludes initial covering of the bowel in a plastic covering (bag or cling film) prior to intervention. *Exomphalos*: surgery or application of topical treatment to the sac in patients managed conservatively (regardless of whether or not they go on to require surgery). *Hirschsprung's disease*: surgery, either temporising or definitive, or rectal/distal bowel irrigation, laxatives or digital stimulation in patients managed conservatively. This does not include pre-operative washouts in patients planned to have surgery. *Anorectal malformation*: surgery, either temporising or definitive, or anal/fistula dilatation in patients with a low anorectal malformation managed conservatively.
American Society of Anesthesiologists Score at the time of primary intervention	1.Healthy person, 2. Mild systemic disease, 3. Severe systemic disease, 4. Severe systemic disease that is a constant threat to life, 5. A moribund patient who is not expected to survive without the operation, Not applicable — no intervention.

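### Parenteral nutrition enters the gastroschisis mortality model with no start time, so babies who die before it could begin can make an ineffective treatment look protective

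*Protocol article*

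**What the plan says.** The primary endpoint is stated under Outcome measures: "The primary outcome is all-cause, in-hospital mortality". Its window is closed for long stays: "For patient’s hospitalised for >30 days following primary intervention, a 30-day post-primary intervention mortality rate will be used".

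The Data analysis section (Patient and institutional data) screens covariates against death by univariate logistic regression. It then reduces a multilevel logistic model by backward elimination to find interventions and peri-operative factors that affect outcome. It says the data will be adjusted for confounders and effect modifiers, and lists among the latter "provision of other condition-specific neonatal care such as parenteral nutrition in neonates with gastroschisis".

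Table 1 gives these answers for parenteral nutrition: "Yes and it was given, Yes and it was sometimes available but less than required, Yes but it was not available, No". The follow-up item on duration reads "Include all days that the patient received parenteral nutrition (any volume) up until 30 days post-primary intervention". Central venous access is recorded in the same way: "Please select all that the patient received within 30 days of primary intervention or 30 days of presentation if no intervention was undertaken". Transfusion and ventilation use the same 30 days. Antibiotics after the intervention are recorded as "Total duration of antibiotics following primary intervention".

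Fluid bolus, warming and antibiotics for sepsis on arrival are different. Table 1 ties each to the first hour or first day after arrival.

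**The concern.** The model has no time axis, and exposure and death share one window. A child must live long enough to receive a treatment that starts later, so receipt is partly a consequence of survival (immortal time bias). Early deaths fall in some category other than 'given', whatever the treatment does.

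The label 'effect modifier' does not keep parenteral nutrition out of the mortality model, because the plan says it adjusts for effect modifiers and is looking for interventions that affect outcome.

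The second objective is at stake: finding modifiable care factors, which the Introduction wants to use for advocacy and to inform interventional studies. Parenteral nutrition in gastroschisis is the plan's own example. A spurious protective association would also tend to pass the p<0.10 screen and survive backward elimination.

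**Working it through.** The plan gives no figure on this point. Its only planning figure for the condition, 15 gastroschisis cases per group, reproduces exactly from 56.6% v 3.7% mortality with 80% power, two-sided alpha 0.05/3 and pooled variance. It is not in dispute.

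**Inputs**
- m, total mortality. Table 2 gives 56.6% for gastroschisis in low and middle income countries combined.
- e, the share of deaths occurring before parenteral nutrition could start. The documents do not give it; assumed 10% to 50%.
- p, uptake among babies alive when it could start. The documents do not give it; 50% assumed, then varied.
- The treatment truly has no effect.

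**Case A: 'given' v 'not available'.** Early deaths at hospitals with parenteral nutrition cannot be 'given'. Early deaths at hospitals without it are coded 'not available'.
- Odds of death, 'given': m(1−e)/(1−m).
- Odds of death, 'not available': m/(1−m).
- Odds ratio = 1−e.

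**Case B: received v not received.** All early deaths join the untreated group.
- Treated: deaths p·m(1−e), survivors p(1−m).
- Untreated: deaths m·e + (1−p)·m(1−e), survivors (1−p)(1−m).
- Odds ratio = (1−e)(1−p)/[e + (1−p)(1−e)], which is (1−e)/(1+e) at p = 0.5.
- Example with m = 0.566, e = 0.3, p = 0.5: treated mortality is 0.1981/(0.1981 + 0.217) = 47.7%; untreated is 0.3679/(0.3679 + 0.217) = 62.9%; odds ratio 0.54.

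**Case C: 'given' v 'not available', with early deaths coded 'No' at every hospital.** Both groups lose the same share of deaths, so the odds ratio is 1.00.

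| e | Case A | Case B (p = 0.5) | Case C |
|---|---|---|---|
| 10% | 0.90 | 0.82 | 1.00 |
| 20% | 0.80 | 0.67 | 1.00 |
| 30% | 0.70 | 0.54 | 1.00 |
| 50% | 0.50 | 0.33 | 1.00 |

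Total mortality m cancels in all three cases, so agreement across the Table 2 mortality figures is an identity and not a robustness check. Uptake does matter in case B. At e = 0.3 the odds ratio is 0.62 for p = 0.3 and 0.32 for p = 0.8. At p = 0.2 it runs from 0.88 (e = 0.1) to 0.44 (e = 0.5).

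**Simulation of case B.** The plan implies about 183 × 0.85 = 156 gastroschisis cases from low and middle income countries. The simulation used 2000 runs, mortality of 56.6%, uptake of 50%, start on day 1 to 3, and median time to death of 3 to 10 days (exponential, truncated at 30 days). Apart from the case count and the mortality, the inputs are assumptions. The null odds ratio ran from 0.33 to 0.88, and the false-positive rate at p<0.05 from 7% to 90%. Restricting to babies alive at the start day gave odds ratios of 0.99 to 1.01 and 4% to 6% rejection.

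**The case against.** The strongest reply is that the form does not ask whether parenteral nutrition was ever received. It asks about need and availability, and does not say how to enter a baby who died before it could start. The odds ratios of 0.82 to 0.33 therefore belong to one way of splitting the answers. This stands: case A is milder and case C shows no bias. The coding rule is unstated, so the size is a range that includes no bias at all.

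A reader might infer that all peri-operative care is biased towards looking protective. The documents do not support that. Arrival fluids, warming and arrival antibiotics are already anchored in time. For central access, transfusion and ventilation, sicker babies tend to receive more, which can push the association the other way.

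A reader might also infer that the plan commits to treatment-duration covariates. It does not name them. It does name peri-operative antibiotics, and Table 1's only antibiotic item following the intervention is a duration, so the caution is worth stating.

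Two further points stand in part. The gastroschisis-specific fields are in supplementary file 1, which is not shown, so the missing start day is established for Table 1 only. The planned adjustment for ASA score, weight and time to presentation, and the hospital level, are not in the figures above. They could change the size but do not supply the missing timing.

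Finally, the plan already has a separate model of institutional factors. That offers a fallback but does not repair the patient-level model.

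**Conclusion.** The concern holds for parenteral nutrition in gastroschisis. The stated model and the Table 1 coding together allow an ineffective treatment to appear protective. With 10% to 50% of deaths assumed to precede its start, the null odds ratio is 0.90 to 0.50 for 'given' against 'not available' and 0.82 to 0.33 for received against not received at 50% uptake. It is about 1.00 in the first comparison if early deaths are coded 'No' everywhere. The documents fix neither the early-death share, nor uptake, nor the coding of early deaths, so no single value should be quoted.

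Central access, transfusion and ventilation have the same timing flaw with an uncertain net direction. It would be wrong to conclude that the primary comparison between income groups is compromised, since it does not use these exposures. What changes is how far the second objective can be answered from patient-level care variables.

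**What to change.** For patient-level models of death on care that starts after the primary intervention, include only children alive at a fixed, pre-stated landmark and report earlier deaths separately. This needs no new field: Table 1 already collects days from admission to death and hours from arrival to primary intervention. Because that second item is entered as 0 when no intervention took place, those children must be identified before the landmark is computed.

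- If the form can still be changed, add a start day for each such treatment and classify exposure by what had begun by the landmark.
- If it cannot, call the restricted analysis a partial correction, because deaths between the landmark and a later start still cannot be coded 'given'. If the institutional survey records availability (it is not shown), use hospital-level availability as the exposure.
- Do not use antibiotic, ventilation or parenteral-nutrition days as covariates for death, since death cuts them short.

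The cost is fewer deaths in those models and, if a start day is added, one extra field per treatment, with the form changes and translations that this brings.
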